#### Analysis

We will use descriptive statistics to describe the baseline characteristics of the groups reported as count (percent) for categorical variables, and mean (standard deviation) or median (first quartile, third quartile) for continuous variables, depending on the distribution. We will adopt Consolidated Standards of Reporting Trials (CONSORT) criteria for reporting on non-inferiority and equivalence trials in reporting the trial [38]. The principal analysis will be per- protocol, as is recommended for non-inferiority trials [39–41]. The principal analysis is not intention-to-treat (ITT) simply because the effect of ITT analysis is to reduce the difference seen between treatment groups; in a superiority trial, ITT analysis functions to buttress a conclusion of superiority, but in a non-inferiority trial it could lead to a false conclusion of non-inferiority by masking a true difference between treatment arms.

We will use logistic regression to analyze binary outcomes, Poisson regression for count outcomes and linear regression for continuous outcomes. Descriptive analyses will be used to compare rates of viral and atypical co-infections in the entire study population and between groups.

We will perform some subgroup analyses by adding an interaction term between treatment group (5-day vs. 10-day course) and the following subgroups: (1) older (age 5–10 years) vs. younger (age <5 years); (2) higher vs. lower salivary CRP; and (3) virus/*Mycoplasma* detected in baseline NPS vs. no virus detected. These interaction tests will be exploratory in nature and not adjusted for multiple testing [42].

These analyses will be exploratory. The following sensitivity analyses are planned: (1) intention-to-treat analysis; (2) strict per-protocol analysis including only those participants who were adherent to their medications and whose radiographs were reported by a radiologist to demonstrate alveolar infiltrates; (3) per-protocol analysis stratified by whether the saliva CRP was greater than the 75th percentile; and (4) per-protocol analysis stratified by whether a virus, an atypical pathogen, or high-level *S. pneumoniae* colonization was found in the NPS. If evidence is found of effect modification or confounding related to the above parameters additional analyses will be undertaken. The results of all analyses will be reported as estimate of effect, corresponding 95% CI and associated *p* values. All *p* values will be reported to three decimal places with those less than 0.001 reported as *p* < 0.001. The criterion for statistical significance will be set at alpha = 0.05. Table 1 provides a summary of the outcomes, corresponding hypotheses, measure, and method of analysis.

**Table 1 Tab1:** Variables, measures, and methods of analysis

Variable/outcome	Hypothesis	Outcome measure	Methods of analysis
Primary			
Clinical cure (per-protocol)	Short-course (5-day) treatment with high-dose amoxicillin is non-inferior to long-course (10-day) treatment	At visit (day 14–21) composite of: 1. Defervesced on or before day 4 2. No more than 1 further fever spike until visit 3. No tachypnoea and decreased work of breathing 4. No additional antibacterials given Dichotomous	Logistic regression
Secondary, between-group comparisons			
Absenteeism (caregiver, from work)	Short-course treatment is non-inferior to long-course treatment	Daily symptom diaries: self-reported number of caregiver-days absent from work (count)	Poisson regression
Absenteeism (child, from daycare/school)	Short-course treatment is non-inferior to long-course treatment	Daily symptom diaries: reported number of child-days absent from daycare/school (count)	Poisson regression
Mild drug adverse reactions	Fewer in short-course arm than in long-course arm	Daily symptom diaries: Reported number of child-days with diarrhoea, rash, abdominal pain, yeast infection (count)	Poisson regression
Anaphylaxis and other severe drug adverse reactions	Fewer in short-course arm than in long-course arm^a^	Daily symptom diaries, SAE reports. Dichotomous	Descriptive statistics
Adherence to study medications	Better in short-course arm than in long-course arm	Daily symptom diaries, RA interview: “adherence” defined as > 80% amoxicillin doses given (<3 doses of initial 15 doses in short-course arm, < 6 doses in reference arm) Dichotomous	Logistic regression
Recurrence of respiratory illness after primary outcome visit but before 30-day follow up	Short-course treatment is non-inferior to long-course treatment	RA interview. Dichotomous	Logistic regression
Development of antibiotic-resistant organism (ARO) colonization	Less frequent in short-course arm than in long-course arm	Enteric swab testing: “new colonization”’ defined as 3–6 month swab ARO positivity in context of baseline swab ARO negativity. Dichotomous	Logistic regression
Disruption of gut microbiome	Less marked in short-course arm than in long-course arm	Enteric swab testing: comparison of gut microbiome at 3–6 months to baseline gut microbiome. Continuous	Linear regression
Tertiary, entire-cohort			
Distribution of salivary C-reactive protein in cohort	Mean will be greater than that observed in children with bronchiolitis but less than that observed in children with empyema	Salivary swab testing: continuous	Descriptive statistics expressed as mean (95% CI)
Prevalence of high-level *S. pneumoniae* nasopharyngeal colonization	Majority of cohort will be positive	Nasopharnygeal swab (NPS) testing: Dichotomous	Percentage, with 95% CI
Prevalence of *Mycoplasma* detection	Minority of cohort will be positive	NPS testing: Dichotomous	Percentage, with 95% CI
Subgroup analyses			
Older (age 5–10 years) vs. younger (age <5 years)	Older age group will have higher salivary CRP values, lower rates of *S. pneumoniae* high-level colonization, more *Mycoplasma* positivity, and decreased rates of clinical cure	Clinical cure (as defined above)	Logistic regression with an interaction term between subgroup and treatment variables
Higher vs. lower salivary CRP	Higher salivary CRP will be associated with decreased rates of clinical cure	Clinical cure	Logistic regression with an interaction term between subgroup and treatment variables
Virus/*Mycoplasma* detected in baseline NPS vs. no virus detected (for primary outcome)	Detection of a virus or *Mycoplasma* will not affect observed rates of clinical cure	Clinical cure	Logistic regression with an interaction term between subgroup and treatment variables
Sensitivity analyses – for primary outcome only			
Intention-to-treat	Results will remain robust	Clinical cure	Logistic regression
Strict per-protocol (those with adherence >80% and radiologist-verified pneumonia)	Results will remain robust	Clinical cure	Logistic regression

*SAE* serious adverse event, *RA* Research Assistant, *ARO* antibiotic-resistant organism, *CRP* C-reactive protein

^a^Too few events expected to be able to observe differences in treatment arms

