#### Follow up

The RA will phone the caregiver once at day 3–5 and once at day 7–10 to verify the clinical stability of the participant. Caregivers will also be explicitly informed that they can contact the study team in the event of a concern prior to the scheduled phone calls. The caregiver will be given a study diary to complete each day, which will include the following: temperature, dyspnoea (older participants), increased work of breathing, school attendance, caregiver absenteeism from work duties, days of mild diarrhoea, mild (abdominal discomfort, rash) and severe (anaphylaxis) drug adverse reactions, and the number of missed medication doses, if applicable. The caregivers will be instructed how to take their child’s temperature and assess increased work of breathing. Any participant who has persistent fever more than 3 days post-enrolment will receive an additional 5 days of open-label amoxicillin after the initial 5 days (i.e. will receive a guaranteed 10 days of antimicrobial agents). Any participant who worsens clinically subsequent to enrolment at any time point prior to the primary outcome visit will be urged to seek medical care without delay either at the site where recruitment took place or with another physician (e.g. family physician, walk-in clinic); all participants will be provided with printed documentation about the SAFER trial and contact information for the local Principal Investigator (PI) for the benefit of the medical professional re-evaluating the participant. The criteria for permanent discontinuation of the experimental aspect of the study protocol in an individual subject are as follows: failure to defervesce by day 4 post-enrolment; requirement for hospitalization because of worsening respiratory illness; severe reaction potentially associated with amoxicillin, such as a generalized allergic reaction (urticarial rash, bronchospasm, angioedema, hypotension, etc.); requirement for prohibited concomitant medications; completion of treatment/intervention as defined by the protocol; or clinical reasons believed by the physician to be life-threatening.

The daily symptom diary will include prompts to aid caregivers to remember the three daily doses of study medication. The RAs will also encourage optimal adherence to medication administration at baseline and at each of the two scheduled follow-up phone communications.

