The participant will return to the hospital at day 14–21 for the measurement of the primary outcome and to deliver the study diaries. At this visit, the RA will verify whether the participant developed new fever or required additional antimicrobials, and will have a physician or nurse perform a brief physical examination (temperature, respiratory rate, and assessment of increased work of breathing). The medication bottles will be returned and the volume of remaining medication determined. The RA will phone the caregiver one month after enrolment to verify continued clinical stability. All attempts will be made to follow up participants, even those who are already known to represent clinical failure (e.g. do not defervesce by day 4 post-recruitment and receive 10 days of open-label amoxicillin) or who receive additional interventions outside of the study (e.g. have additional antimicrobial agents prescribed by other clinicians) to ensure completeness of data collection (Fig. 1).

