All serious AEs (SAEs) that are both unexpected and related to the study product will be reported to Health Canada, and those related to the study product or procedures will be reported to the appropriate REB as soon as possible if required by the REB, but no later than 15 calendar days (7 days if fatal or life-threatening) after first knowledge of the event. Further information and significant new information on ongoing reported SAEs will be provided to the sponsor, the REB and Health Canada, as applicable. Copies of all information about the SAE will be kept in the regulatory binder.

All caregivers will be asked to complete a symptom diary form each day post-randomization until the tenth post-randomization day; questions on this form will seek information on clinical features of persistent or worsening respiratory disease (e.g. fever, difficulty breathing, overall clinical status) in addition to common (e.g. diarrhoea) and serious (e.g. anaphylaxis) AEs known to be associated with amoxicillin administration. In addition, the RA will specifically ask about symptoms and signs consistent with respiratory deterioration or amoxicillin-associated AEs. This will also be done at the time of visit 1, when the participants return to be clinically evaluated at day 14–21 post-randomization.

The SAE most likely to occur is hospitalization in the first few days post-recruitment, due to worsening respiratory status. Though the majority of children with mild CAP respond well to oral antimicrobial therapy, a small percentage will worsen and require admission to hospital because of progressive oxygenation failure and/or the need for operative drainage of pleural-based collections. These SAEs would not be related to any trial procedures, as all study participants will be receiving the first-line antimicrobial agent of choice (high-dose amoxicillin) for the first 5 days post-enrolment. We note that the risk of harm to trial participants will likely be less than to non-participants, because study staff will be contacting all study participants at intervals to verify clinical stability. As detailed above, the RAs will contact all study participants once at day 3–5 post-recruitment and once at day 7–10 post-recruitment and will be actively questioned about symptoms indicative of worsening respiratory status. Furthermore, all participants that are persistently febrile at day 4 post-recruitment will complete 10 days of open-label high-dose amoxicillin.

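### Non-inferiority is decided on the per-protocol analysis only, although events that end protocol treatment are themselves primary-outcome failures; the intention-to-treat (ITT) result should be required to agree

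*Protocol article*

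**What the plan says.** **Which analysis decides.** Under Analysis, the protocol article says: "The principal analysis will be per- protocol, as is recommended for non-inferiority trials". The primary row of Table 1 is likewise labelled per-protocol. The Sample size section concludes non-inferiority when the upper bound of the one-sided 97.5% confidence interval for the failure difference is below 7.5 points.

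**What ITT is for.** "The following sensitivity analyses are planned: (1) intention-to-treat analysis". Table 1 expects the result to remain robust and says nothing about what follows if it does not. A second sensitivity analysis is a "strict per-protocol analysis including only those participants who were adherent to their medications"; it also requires a radiologist's reading of alveolar infiltrates.

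**The reason given.** The Analysis section argues that ITT shrinks differences between arms and so could produce a false finding of non-inferiority.

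**Events that end protocol treatment.** The Follow up section says: "Any participant who has persistent fever more than 3 days post-enrolment will receive an additional 5 days of open-label amoxicillin". It then gives a list that begins "The criteria for permanent discontinuation of the experimental aspect of the study protocol in an individual subject are as follows" and includes failure to defervesce by day 4 and hospitalisation for worsening respiratory illness.

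**The same events as outcomes.** The Follow up section plans continued data collection for all enrolled children, with this remark: "even those who are already known to represent clinical failure (e.g. do not defervesce by day 4 post-recruitment and receive 10 days of open-label amoxicillin". In Table 1, the per-protocol outcome requires defervescence by day 4. The Primary outcome section counts hospital admission for persistent or progressive lower respiratory illness as failure.

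**The concern.** The case against ITT in a non-inferiority trial is familiar, but it is half of the argument. ITT can dilute a difference through non-adherence and crossover. A per-protocol analysis can distort one by removing children for reasons related to how they fared, and it then no longer compares the groups as randomised. Neither set is conservative in all circumstances, which is why agreement between the two is the usual safeguard.

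The general point has particular force here because two of the events that stop the experimental part of the protocol are also failures on the primary outcome. Any per-protocol rule that treats stopping, or receiving additional amoxicillin, as a ground for exclusion would remove failures.

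The fever rule adds a possible asymmetry. A child with persistent fever receives 10 days of amoxicillin whatever the allocation. Ten days departs from the 5-day regimen but matches the 10-day regimen. A rule based on duration received would therefore take these failures out of the short arm and leave them in the long arm. With an expected failure rate near 5%, a handful of children would matter, and as the decision rule stands a contrary ITT result would not change the conclusion.

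**Working it through.** **1. The plan's own figure.** Inputs from the Sample size section and the abstract: 5% failure in the reference arm, margin 7.5 points, one-sided alpha 0.025, power 80%. I assume 5% failure in the 5-day arm as well.

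- n per arm = (1.960 + 0.842)² × 2 × 0.05 × 0.95 / 0.075² ≈ 133, against the stated 135.
- At 135 per arm, SE = √(2 × 0.05 × 0.95 / 135) = 2.65 points, and power = Φ(0.075/0.0265 − 1.96) ≈ 81%.

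The stated sample size is reproduced and is not in dispute.

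**2. Overlap between stopping events and the outcome.**

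| Event | Ends the experimental part (Follow up) | Failure on the primary outcome |
|---|---|---|
| No defervescence by day 4 | Yes | Yes (Table 1; Follow up) |
| Hospitalisation for worsening respiratory illness | Yes | Yes (Primary outcome) |

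**3. Illustration of one-sided exclusion.** The documents do not give the share of children who fail early. Let q be that share, assumed to be 1 to 3 points of the 5% and equal in both arms. In 135 children that is 135 × 0.01 ≈ 1.4 to 135 × 0.03 ≈ 4.1. If these children left the 5-day arm only, its failure rate p would become (p − q)/(1 − q), while the 10-day arm would stay at 5%.

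| q | True rates 12.5% vs 5% (excess 7.5) | True rates 5% vs 5% (excess 0) |
|---|---|---|
| 1% | 0.115/0.99 − 0.05 = 6.6 points | 0.04/0.99 − 0.05 = −1.0 points |
| 2% | 0.105/0.98 − 0.05 = 5.7 points | 0.03/0.98 − 0.05 = −1.9 points |
| 3% | 0.095/0.97 − 0.05 = 4.8 points | 0.02/0.97 − 0.05 = −2.9 points |

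**4. Effect on the error rate.** A simulation (200,000 trials, 135 per arm, Wald 97.5% bound, true rates 12.5% and 5%) gives the chance of wrongly concluding non-inferiority:

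| Early-failure share | Kept as failures in both arms | Removed from both arms | Removed from 5-day arm only |
|---|---|---|---|
| 1% | 3.2% | 3.2% | 5.6% |
| 2.5% | 3.3% | 3.2% | 11.9% |
| 4% | 3.2% | 3.7% | 23.9% |
| 5% | 3.3% | 5.4% | 35.6% |

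The last two rows assume that nearly all, or all, failures in the reference arm occur early, and mark the extreme of the range. The first column exceeds 2.5% because the Wald bound is approximate at these rates. The serious inflation comes from asymmetric removal.

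**5. What requiring both sets does.** The chance that both analyses fall below the margin cannot exceed the chance that ITT alone does. In this simulation, the column with children kept as failures in both arms plays the part of ITT, so the joint rule holds the false conclusion at about 3.2 to 3.3% however the per-protocol set is drawn.

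**The case against.** The strongest objection is that the article nowhere describes one-sided removal. A reader might infer from the fever rule that failing children leave the 5-day arm and stay in the 10-day arm. The documents do not support that reading:

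- The fever rule is part of the protocol and applies to any participant in either arm, so a child managed under it has followed the protocol.
- The Follow up section describes these children as clinical failures and keeps them in follow-up.
- The per-protocol outcome in Table 1 contains defervescence by day 4 as a component. Excluding the children who miss it would empty that component.
- Adherence restricts only the strict per-protocol sensitivity set. It is also a floor on doses given, not a ceiling, so additional open-label amoxicillin would not breach it.
- Stopping the experimental part is not the same as leaving the analysis. The same list includes completing treatment as planned.
- Hospitalised children are not said to receive 10 days of amoxicillin, so the argument from matching duration covers only the fever rule.

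All of this stands. Exact membership of the per-protocol set may also properly be left to the full protocol or analysis plan, so its absence from an article is not itself a fault. The figures in steps 3 and 4 of the working rest on an assumed exclusion rule as well as an assumed early-failure share.

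The objection does not reach the decision rule. The article itself makes per-protocol the sole basis for the conclusion, argues against ITT in that role on one-sided grounds, and attaches no consequence to disagreement. It is fair to say that ITT is planned and will be reported; it simply carries no weight in the conclusion.

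**Conclusion.** The point holds as a weakness in the stated decision rule. Per-protocol is the only decisive analysis, ITT cannot alter the conclusion, and the justification overlooks that exclusions here can be linked to outcome and can also push towards non-inferiority.

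It does not hold as a claim that the plan drops failures from one arm. The text leans towards counting them as failures in both, and under that handling the bias disappears. The shift from 7.5 to between 6.6 and 4.8 points illustrates what is at stake if the set were drawn by duration received, with early failures assumed at 1 to 3 points. It is not an estimate of bias in the trial as written. The sample size is unaffected.

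This is a cheap improvement to the plan.

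**What to change.** 1. Change the decision rule: conclude non-inferiority only if the upper bound of the one-sided 97.5% interval is below 7.5 points in both the per-protocol and the ITT analysis.
2. Add one confirming sentence: a child who meets a failure criterion, or who receives open-label amoxicillin or other antibacterials because of it, stays in the per-protocol set as a failure in the allocated arm.

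If the sponsor already intends the second, the sentence merely records it. Neither change touches treatment, follow-up or the number randomised. The cost is protocol or SAP wording and a small loss of power from requiring two analyses to succeed. The size of that loss depends on how many children the per-protocol set excludes, which the article does not give.

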**Methods:**

The objective of this multicentre, randomized, non-inferiority, controlled trial is to investigate whether 5 days of high-dose amoxicillin is associated with lower rates of clinical cure 14–21 days later as compared to 10 days of high-dose amoxicillin, the reference standard. Recruitment and enrolment will occur in the emergency departments of McMaster Children’s Hospital and the Children’s Hospital of Eastern Ontario. All children in the study will receive 5 days of amoxicillin after which point they will receive either 5 days of a different formulation of amoxicillin or a placebo. Assuming a clinical failure rate of 5% in the reference arm, a non-inferiority margin of 7.5%, one-sided alpha set at 0.025 and power of 0.80, 270 participants will be required. Participants from a previous feasibility study (n = 60) will be rolled over into the current study. We will be performing multiplex respiratory virus molecular testing, quantification of nasopharyngeal pneumococcal genomic loads, salivary inflammatory marker testing, and faecal microbiome profiling on participants.

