### Study procedures

#### Screening, enrolment, and randomization

Attempted recruitment will be triggered in the ED as soon as a child of the appropriate age is diagnosed with CAP by the ED physician during study hours. All participants will be provided with the appropriate medications and nasopharyngeal, salivary, and enteric specimens will be collected; note that participants can opt out of providing any of these specimens and still participate in the trial. The interpretation of the chest radiograph by the radiologist will be abstracted and recorded.

All eligible participants will be assigned a study ID. Randomization of the participants will be completed using a randomization scheme (stratified by site) generated by the study pharmacy at MCH using a random number generator, using block sizes of 2 and 4, and will pre-assign kit contents to a given study ID. The RA will notify the site study pharmacy after a successful recruitment and will communicate the study ID so that the appropriate medications can be prepared by the research pharmacist; for the duration of the study, the pharmacist will be the only individual not blinded to the participant’s treatment allocation. All participants will be given an initial 5 days of amoxicillin to begin. For potential participants at MCH who present at a time when an RA is not available, the attending ED physician will prescribe amoxicillin at the study dose (i.e. the standard of care) and obtain consent for subsequent RA contact and potential enrolment within 24 h after ED discharge. Recruitment at CHEO will only proceed between 10.00 a.m. and 10.00 p.m. daily. Participants will be given all study medications at enrolment unless a participant presents outside of pharmacy operational hours at MCH; in that instance, the RA will dispense an after-hours open-label amoxicillin kit for the first 5 days of treatment to the caregiver and contact the pharmacy with the study ID so that the blinded medication kit can be prepared and provided to the caregiver at a later date (prior to day 6).

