### Statistical analysis

#### Sample size

We estimate the baseline failure rate of standard therapy to be ~ 5%; this estimate is consistent with previous studies in children [13], is less than in similar adult studies [7], and is the approximate rate that was seen in the pilot study. We will use a non-inferiority margin of an additional 7.5%. As this is a non-inferiority trial, the crucial statistical comparison will be between the 97.5% (one-sided) CI of the difference between the failure rate of the experimental arm and the standard therapy arm; should the upper bound of this difference be smaller than 7.5%, a conclusion of non-inferiority will be reached. As the maximum baseline failure rate in the reference arm is probably 5%, the maximum failure rate in the experimental arm that would still be felt to be “non-inferior” would be 12.5%; the margin of 7.5% was selected to make the maximum failure rate in the experimental arm less than 13.5%, the median acceptable failure rate in the treatment of CAP identified in a survey of infectious-disease physicians [37]. Setting α at 5%, with 80% power, 135 participants in each arm will be required for this trial (PASS software package, NCSS LLC, Kayesville, UT, USA); as we will have accrued ~ 60 subjects in the pilot to be “rolled over”, an additional 210 participants will be required. Our experience conducting the pilot, combined with an analysis of visits to the EDs of the study sites, leads us to believe that this target should be achievable. It is estimated that the target sample size should be attainable after 2 years of enrolment.

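### The success rule is a 7.5-point difference in failure rates, but the named primary method is logistic regression, whose treatment effect is an odds ratio, and the article states no link between them

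*Protocol article*

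**What the plan says.** Under Statistical analysis, Sample size, the article places everything on the absolute scale. The margin is "We will use a non-inferiority margin of an additional 7.5" percentage points, the deciding comparison concerns "the 97.5% (one-sided) CI of the difference between the failure rate of the experimental arm and the standard therapy arm", and "should the upper bound of this difference be smaller than 7.5%, a conclusion of non-inferiority will be reached". The abstract gives the design inputs: "Assuming a clinical failure rate of 5% in the reference arm", with "one-sided alpha set at 0.025 and power of 0.80, 270 participants will be required".

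The Analysis section then assigns methods by type of outcome: "We will use logistic regression to analyze binary outcomes, Poisson regression for count outcomes and linear regression for continuous outcomes". Table 1 lists logistic regression for clinical cure (the primary row) and again for the intention-to-treat and strict per-protocol sensitivity analyses. The text before Table 1 promises an effect estimate with a 95% interval and does not name the measure.

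Randomisation is done "using a randomization scheme (stratified by site"). The Analysis section names no covariates for the main comparisons.

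**The concern.** The treatment coefficient of a logistic model is a log odds ratio. Its confidence limit cannot be set against 7.5 percentage points without a further step, and the article describes no such step. The rule that decides the trial and the method named for the primary outcome are therefore on different scales.

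In a non-inferiority trial this matters more than a reporting detail would. The two scales can give opposite verdicts on the same data. They also drift apart when the control failure rate is not the assumed 5%. If the link is left open until the data are seen, the choice of scale could be made, or be suspected of having been made, in the light of the result.

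**Working it through.** **Inputs.** Control failure 5%, margin 7.5 points, one-sided alpha 0.025, power 80%, 135 per arm (abstract and Sample size section). Sample size also gives alpha as 5%, which agrees with the abstract only if read as two-sided. Assumptions not stated in the article: 5% true failure in both arms, and no losses or per-protocol exclusions.

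**1. The plan's own figure.** On the risk-difference scale with unpooled variance:

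n per arm = (1.960 + 0.8416)² × 2 × 0.05 × 0.95 / 0.075² = 7.849 × 0.095 / 0.005625 = 132.6, so 133 per arm. This is within 2% of the stated 135.

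Power at 135: SE = √(0.095/135) = 0.02653, and Φ(0.075/0.02653 − 1.96) = 80.7%. Exact binomial enumeration of the Wald rule gives 81.5%. The design was therefore sized for a risk-difference test.

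**2. The same margin as an odds ratio.**

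- Equivalent margin at 5%: (0.125/0.875)/(0.05/0.95) = 2.714, and ln 2.714 = 0.9985.
- SE(ln OR) = √(2/(135 × 0.05 × 0.95)) = 0.558.
- Power = Φ(0.9985/0.558 − 1.96) = 43.2%. Exact enumeration gives 41.6%, or 45.7% with 0.5 added to each cell.
- n per arm for 80% power = 7.849 × 2/(0.0475 × 0.9985²) = 332.

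**3. How often the scale changes the verdict.** With 5% failure in both arms, the Wald risk-difference rule and the 2.714 odds-ratio rule disagree in about 40% of trials by exact enumeration. Almost always the risk difference passes and the odds ratio fails. Two illustrations:

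- With 7/135 failures in each arm, the upper bound of the difference is 1.96 × √(2 × 0.0519 × 0.9481/135) = 5.3 points (pass). The upper bound of the odds ratio is exp(1.96 × √(2 × (1/7 + 1/128))) = 2.93 (fail).
- With 7 control failures, the risk-difference rule accepts up to 9 failures in the 5-day arm and the odds-ratio rule up to 6.

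**4. Drift with the control rate.** A fixed odds ratio of 2.714 corresponds to 3.2 points at a 2% control rate and 13.2 points at 10%.

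**5. Can a logistic fit supply the risk difference?** Yes. For 9/135 against 6/135, the two-arm logistic model gives predicted risks that differ by 2.22 points, with delta-method SE 0.02785. That equals the ordinary Wald SE of the difference. In the unadjusted case no power is lost.

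**6. Choice of interval for the risk difference** (135 per arm, exact enumeration, unstratified):

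| Interval | Power, 5% in both arms | One-sided error, 12.5% vs 5% |
|---|---|---|
| Wald | 81.5% | 3.3% |
| Miettinen-Nurminen | 74.1% | 2.2% |
| Newcombe | 74.4% | 2.5% |

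At a 2% control rate (9.5% vs 2%), the Wald error rises to about 4.4%, while both score-type intervals stay at about 2.2%. In line with this, a Farrington-Manning calculation asks for 163 per arm, not 135.

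**The case against.** Three points on the other side carry weight.

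- **The model can deliver the test.** A reader might infer that logistic regression is incapable of the planned comparison. It is not: step 5 shows that the risk difference and its standard error follow from the fitted model. The article also never says that the odds ratio is the reported measure.
- **No odds-ratio margin is proposed.** A reader might take 42% as the power of this trial. The article keeps the decision on the difference in failure rates, and for that rule the sample size reproduces. The 42% and the 332 per arm describe only what would follow if the gap were closed the wrong way.
- **An article condenses.** Link function, standardisation, interval method and covariates are commonly left to an analysis plan, which is not shown here. This disposes of any claim that the analysis ignores site: the article is silent on covariates, and silence is not an error.

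What remains is that the article is not silent on the primary method. It names one, in the text and in three rows of Table 1, and that method's direct output does not fit the article's own success rule. An analysis plan may supply the link, but the published statement would still need to agree with it.

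**Conclusion.** The point holds as a mismatch between a stated rule and a stated method, with no link given. It does not make the planned test impossible or underpowered: the risk-difference rule has about 80% power by the Wald calculation on which the sample size appears to rest. The size of the problem is the room it leaves for choice. Settling on the odds-ratio scale would cut power to about 42% and would reverse the verdict in about 40% of trials when the arms are truly equal.

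These figures assume 5% failure in both arms, 135 analysed per arm, and a margin converted at 5%. If the margin is reconverted at each rate, odds-ratio power (normal approximation) runs from 46% at a common rate of 3% to 36% at 10%. Risk-difference power over the same range runs from 95% to 54%. The gap is therefore present throughout, though its size depends on the true rate.

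**What to change.** In the Analysis section and in the primary, intention-to-treat and strict per-protocol rows of Table 1, name the risk difference in clinical failure (5-day minus 10-day), stratified by site to match the randomisation, with a named confidence-interval method. State that its upper one-sided 97.5% limit is compared with 7.5 points. Alternatively, keep logistic regression, include site, and state that the risk difference and its limit come from marginal standardisation. In either case, report the odds ratio as supportive only, and make the change before unblinding.

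The cost is wording, with no new data, but one consequence must be stated. A Miettinen-Nurminen or Newcombe interval controls the error rate better than Wald but gives about 74% power at 135 per arm with 5% failure assumed in both arms. If such an interval is chosen, the stated 80% should be restated. If Wald or the unadjusted delta method is kept, its one-sided error of about 3.3% at a 5% control rate should be acknowledged.
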